### Computation of sample size

The main aim of the study is to assess the relative efficacy of a specific EMDR intervention protocol versus ST therapy in the clinical stabilization (decrease in the risk of relapse) of traumatized bipolar patients. For this reason the reduction of the risk of relapse after treatment with a follow-up of 24 months will be used as the dependent variable of the study. The calculation of the sample size was based on a survival analysis using the statistical package “powerSurvEpi” for R (http://www.r-project.org/) using an alpha = 0.005 instead of 0.05 to allow correction for multiple comparisons. The number of patients required to detect a hazard ratio = 2 (i.e., the hazard rate of relapse is one group is the double of the hazard rate in the other group) in a Cox regression with a statistical power of 80% and alpha = 0.005 is *n* = 36 per intervention group (two groups, EMDR and ST, equals to a total *n* = 72). According to Chambless and Hollon (1998) a sample of this size should show clinically relevant differences [27]. Assuming a percentage of dropouts of about 10–15% of the participants it would be necessary to recruit approximately 82 patients, 41 allocated in each intervention arm.

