### Study aim

The overall aim of this study is to examine whether the EMDR Bipolar protocol for BP with a history of traumatic events can reduce affective relapses, improve affective and trauma-related symptoms and result in a better performance in cognition and psychosocial functioning, when compared ST. Other related aims of this trial are to expand the available options for psychosocial intervention in BD, to explore that the EMDR therapy is a safe and effective tool in traumatized bipolar patients and that treatment with EMDR leads to an improvement in the course and prognosis of the disease.

Based on our pilot study of EMDR in traumatized bipolar patients, we propose the following hypotheses:The EMDR group will show fewer affective relapses at 12 and 24 months’ follow-up compared to the ST groupPatients in the EMDR group will show fewer affective and trauma-related symptoms compared to the ST group at evaluations after 6 months of therapy, at 12 and 24 monthsPatients in the EMDR group will show a better cognitive and psychosocial functioning compared to the ST group at evaluations after 6 months of therapy, at 12 and 24 months

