### Trial design

This is a single-blind, randomized controlled clinical trial with two parallel branches, EMDR and ST. Patients will be matched for age, sex, illness duration and number of affective episodes the year before the clinical trial. The primary outcome variables that are affective relapses, symptoms of trauma and cognition and psychosocial functioning, will be assessed at six time points; pretreatment (T0), mid-treatment at 2 weeks (T1) and at 3 months (T2), post treatment at 6 months (T3), and follow-up evaluations at 12 (T4) and 24 months (T5) (see Fig. 1). The secondary outcome variables that are the course and prognosis of the disease, will be assessed in follow-up evaluations at 12 (T4) and 24 months (T5). The research assistants conducting the clinical assessments will be blind to the participants’ research condition. Patients are not blind to treatment as it is impossible for a therapist to offer and for a patient to receive therapy without being aware of the techniques that they are using orreceiving. The study has been approved by the Ethics Committee of the Germanes Hospitalàries del Sagrat Cor de Jesús (reference number: PR-2014-15), the Hospital Clínic of Barcelona (reference number: HCB/2015/1005) and the Hospital del Mar (reference number: 2015/6502/l). All participants will sign informed consent prior to enrollment. Details of the trial design can be also gathered from Additional file 1 (Standard Protocol Items: Recommendations for Interventional Trials (SPIRIT) flow diagram) and the SPIRIT Checklist (Additional file 2).

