### Interventions

#### Eye Movement Desensitization and Reprocessing (EMDR)

EMDR is a psychotherapeutic approach designed to alleviate the distress associated with traumatic memories facilitating the access and process of traumatic memories and other adverse life experience to bring these to an adaptive resolution. The EMDR therapy will consist of 20 individual sessions 60 min each over a period of 6 months. As stated before, the EMDR Bipolar protocol will include an evaluation of the psychiatric history of the patient and an assessment of dysfunctional cognitions and identification of targets in the context of traumatic events. In addition, the reprocessing of traumatic events will follow the standardized protocol of Shapiro [19] together with the five subprotocols specific for BD that target the following areas:
*Mood stabilization*: the major goal in the treatment process of bipolar patients is the long-term normalization of mood. The aim of this protocol is to reinforce the positive experiences of affective stability and self-control in bipolar patients. Via bilateral stimulations this protocol uses also positive cognitions to strengthen the adaptive system of beliefs. When this installation is reinforced repeatedly, patients are expected to experience an improvement in their self-esteem and affective stability that, in turn, is connected with positive body sensations
*Treatment adherence*: poor adherence in bipolar patients is mainly caused by the feeling of being controlled by drugs, (hypo)manic episodes, lack of insight, a negative view on pharmacological treatment, substance abuse, lack of treatment response and side effects such as weight gain and sedation [27]. This protocol aims to identify and improve those issues and strengthen adherence to avoid further affective relapses. First, we find out what subjective problems are connected to the psychopharmacological treatment. Then, the therapist suggests various positive consequences from taking medication. These are then connected to positive cognitions, emotions or body sensations, and installed via bilateral stimulation

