### Assessments

Demographical and clinical variables will be collected through an interview using the medical history of the patients and a specific Case Report Form (CRF) for the study, including sex, age, age of onset of the disorder, number of relapses, number of previous episodes, history and number of suicide attempts previous and current pharmacological treatment, family background and consumption of drugs. To ensure privacy of participants and safe data storage, data will also be entered in a data file anonymously; participants will be given a unique number, and only the research assistant will be able to link the number with the name of the patient. At baseline (T0) research assistants will also assess clinical severity of affective symptoms, presence of traumatic live events and trauma symptoms, and cognitive and psychosocial functioning. At 2 weeks (T1) and 3 months (T2) of treatment patients will be evaluated with respect to clinical symptoms. After the treatment phase (T3) subjects will be interviewed with respect to clinical symptoms, trauma scales, cognitive and psychosocial functioning and patient satisfaction. During two follow-up visits at 1 year (T4) and 2 years (T5), blind-to-treatment evaluators apply clinical affective and trauma scales, functioning and cognition. See Fig. 1 (flow diagram of enrollment, intervention and assessments).

The clinical severity will be assessed by means of different instruments (see Table 1):

**Table 1 Tab1:** Measurements to evaluate clinical variables

Clinical variable	Measurement interview/Self-report	T0	T1	T2	T3	T4	T5
		Baseline	Mid-treatment		Post treatment	FU 12 months	FU 24 months
Mania	Young	x	x	x	X	x	x
Depression	BDRS	x	x	x	X	x	x
Severity	CGI-BP-M	x	x	x	X	x	x

*FU* Follow-up, *YMRS* Young Mania Rating Scale, *BDRS* Bipolar Depression Rating Scale, *CGI-BP-M* Clinical Global Impression Scale modified for bipolar disorder

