## Statistical analysis

The baseline distribution of sociodemographic and clinical characteristics in each treatment arm will be reported using descriptive statistics.

The main hypothesis of the change in the time to relapse (in weeks) will be analyzed using Cox regressions, and the hypotheses of the changes in the scores of clinical scales as compared to baseline will be tested using repeated measures analyses of variance (ANOVAs) that will include time, treatment arm and their interaction. Those variables that show statistically significant between-arm differences at baseline will be added as covariates in the Cox regressions and repeated measures ANOVAs. For each of the analyses effect size measures (hazard ratio or Hedges’ *g*) will be estimated.

An intention-to-treat (ITT) analysis will be employed to provide unbiased comparisons among the treatment groups, using multiple imputations to deal with the losses of follow-up.

R software will be used to carry out the statistical analyses.

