
To understand better the relationship between the presence of traumatic events and BD, we will study several variables before, during and after treatment. We will assess clinical severity, cognitive and overall functioning variables with specific and validated instruments.

This study aims to replicate the positive results of our pilot study in a larger sample of BD patients, thus strengthening the role of EMDR as a therapy and providing a fast and safe additional tool to established psychosocial interventions that are currently available in the treatment of BD. Strengths of this trial include an innovative, relatively new psychotherapeutic tool (which fills a striking lack of data in the field), a solid methodology and a large observational period of 2 years. The results of this trial are expected to spawn several publications in high-impact factor journals and, if the treatment is useful, will be integrated in future clinical treatment guidelines for BD.

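### The primary outcome is worded as relapse after treatment with 24 months of follow-up, but the schedule most naturally leaves 18 months after treatment, and the wording invites a relapse clock that leaves out relapses occurring after randomisation

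*Protocol article*

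**What the plan says.** The protocol article touches the relapse clock in several places.

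- **Computation of sample size:** "the reduction of the risk of relapse after treatment with a follow-up of 24 months will be used as the dependent variable".
- **Trial design:** pretreatment, 2 weeks and 3 months come first, then "post treatment at 6 months (T3), and follow-up evaluations at 12 (T4) and 24 months (T5".
- **Assessments:** "During two follow-up visits at 1 year (T4) and 2 years (T5") the evaluators apply the scales. The tables label these visits as 12- and 24-month follow-up and give no origin.
- **Interventions:** "The EMDR therapy will consist of 20 individual sessions 60 min each over a period of 6 months"; supportive therapy (ST) runs equally long.
- **Discussion:** the trial's strengths include "a large observational period of 2 years".
- **Study aim:** "The EMDR group will show fewer affective relapses at 12 and 24 months", with no restriction to the period after treatment.
- **Statistical analysis:** "The main hypothesis of the change in the time to relapse (in weeks) will be analyzed using Cox regressions". No time zero is given. The same section promises an intention-to-treat analysis with multiple imputation for losses to follow-up.
- **Dropouts and follow-up:** a relapse with hospital admission in the 6 treatment months takes the patient out of the trial as a dropout. The same event during follow-up does not.
- **Randomization procedure:** allocation follows T0.

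**The concern.** The sample-size section gives the outcome an origin (after treatment) and a length (24 months) that do not both fit a schedule ending at month 24 from T0. Taken at its word, it starts the clock at about T3. The dropout rule points the same way, because it removes some relapses in the treatment months instead of counting them.

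A clock from randomisation and a clock from T3 are two different primary results from the same data. With a T3 clock, relapses in the first 6 months after randomisation do not count. If the patients who had them also leave the risk set, the comparison is conditional on an outcome that treatment may have changed. An effective therapy would keep more high-risk EMDR patients relapse-free to T3, and the later hazard ratio would be pulled towards 1.

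**Working it through.** **Timing.** The visits at 2 weeks, 3 months and 6 months can only be counted from the start, and 12 and 24 months continue the same list. Post-treatment time is then 24 − 6 = 18 months. A full 24 months after treatment would need a visit at 6 + 24 = 30 months. None is scheduled on this axis, and month 30 would exceed the 2-year observation period in the Discussion.

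**Inputs for the illustration.** Relapse rates from the article: almost 70% relapsing within 2 to 4 years (Background), taken as 70% of ST patients by month 24 or by month 48; and two to six episodes in the year before entry (Participants), taken as 2 or 4 a year under ST. Assumptions: individual hazard ratio 0.5 (EMDR/ST), constant individual hazard h, equal arms, and gamma-distributed risk between patients with mean 1 and variance v from 0 to 1. The documents give no value for v.

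**Share of first relapses in months 0–6.** Relapse-free proportion at t months: S(t) = exp(−ht) for v = 0, and (1 + v·h·t)^(−1/v) otherwise, with h halved for EMDR.

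- 70% by month 24, v = 0: by month 6, 26.0% of ST and 14.0% of EMDR patients; by month 24, 70.0% and 45.2%. Share = 40.0/115.2 = 35%. With v = 1 it is 48%.
- 70% by month 48, v = 0: (14.0 + 7.2)/(45.2 + 26.0) = 30%. With v = 1 it is 39%.
- 2 a year, v = 0: (63.2 + 39.3)/(98.2 + 86.5) = 56%. At 4 a year, v = 0: 76%; with v = 1, 69%.

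**Large-sample Cox hazard ratio**, solved numerically from these marginal hazards:

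| ST relapse rate | v | From randomisation to month 24 | From T3, relapse-free only | From T3, all patients kept, next relapse counted |
|---|---|---|---|---|
| any | 0 | 0.50 | 0.50 | 0.50 |
| 70% by month 24 | 0.5 | 0.56 | 0.59 | 0.55 |
| 70% by month 24 | 1 | 0.62 | 0.69 | 0.61 |
| 2 a year | 1 | 0.65 | 0.75 | 0.63 |
| 4 a year | 1 | 0.67 | 0.82 | 0.66 |

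The pull towards 1 appears only in the fourth column and grows with v. Keeping all patients from T3 gives no attenuation relative to randomisation.

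**Events and power.** With 41 per arm, 70% by month 24, v = 0 and no dropout, first relapses from randomisation are 41 × (0.700 + 0.452) = 47. About 10.7 (ST) and 5.7 (EMDR) fall in months 0–6, which leaves 31 from T3 among the relapse-free. Power by the Schoenfeld formula, Φ(√(D/4)·ln 2 − 2.807) at two-sided alpha 0.005, is 34% for D = 47 and 19% for D = 31. At 70% by month 48, events fall from 29 to 21 and power from 18% to 11%. The low starting level is a separate matter, since the planned 72 patients do not give 80% power at alpha 0.005 even if all relapse (51–55%). Only the drop belongs to this point.

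**The case against.** The strongest defence is that the phrase is loose. It sits in a sentence explaining the basis of the sample size and may mean only relapse under a treatment, followed for 24 months. Study aim and Statistical analysis restrict nothing to the post-treatment period, and the visit list and the 2-year period fit a window from baseline to month 24. The exact time origin may also be left to an analysis plan that is not shown. Much of this stands. A reader might infer a proven contradiction, but no section states outright that T5 is counted from T0, and the table labels could be read from the end of treatment. The missing time zero alone would be no finding. What remains is what the article does fix: an outcome worded as post-treatment, a duration that does not fit the natural schedule, and a dropout rule that makes the post-treatment reading a live one.

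Three stronger readings are tempting and are not supported.

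- That a post-treatment clock discards the randomised comparison. It conditions on a post-randomisation outcome only if earlier relapsers leave the risk set. The sample-size section states no such rule, and the dropout rule covers only relapses with admission.
- That most first relapses fall in the treatment months. This holds if the entry rate of 2 or more a year continues. That rate is a selection criterion for patients who are in remission or subsyndromal at entry. At the Background rate the share is 30–48%.
- That the choice of clock could be made after the data are seen. The article cannot show this, because an analysis plan may settle it.

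**Conclusion.** The point holds as a wording conflict on the primary outcome with a real analytic consequence. On the natural reading, post-treatment follow-up is 18 months, not 24. Following the sample-size and dropout sections as written would leave out relapses that occur after randomisation, which does not sit with the intention-to-treat promise.

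The size depends on assumptions. At the Background relapse rates, 30–48% of first relapses would be left out, and 56–76% at 2 to 4 relapses a year. If early relapsers leave the risk set, the largest shift shown is 0.62 to 0.69 at the Background rates and 0.67 to 0.82 at 4 a year, both at frailty variance 1. With no heterogeneity, or with all patients kept from T3, there is no attenuation. The loss of events does not need heterogeneity: about 47 to 31, or 29 to 21 at the lower rate. The point should be corrected, but it does not by itself invalidate the design.

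**What to change.** 1. In Computation of sample size, state the primary outcome as time from randomisation to first affective relapse, up to month 24 (6 months of treatment plus 18 months of follow-up).
2. In Trial design and the table headings, date T4 and T5 as 12 and 24 months from randomisation.
3. In Statistical analysis, name randomisation as time zero of the Cox regression. Count every affective relapse from then on as an event in the primary intention-to-treat analysis, including those with hospital admission during treatment.
4. Reconcile Dropouts and follow-up with this. The change concerns analysis status only: a relapse that has been observed is an event, not a loss to follow-up. Clinical handling is not touched.
5. Report relapse from T3 onwards as supportive only, and say that it is not a comparison of the groups as randomised if earlier relapsers are left out.

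The cost is wording in four places. The post-treatment follow-up must then be given as 18 months, which is less favourable than the 24 now stated. If T5 was in fact meant as 24 months after treatment, the schedule and the 2-year observation period need correcting instead. Time zero should still be randomisation.

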**Discussion:**

The results of this study will provide evidence whether a specific EMDR protocol for patients with BD is effective in reducing affective episodes, affective symptoms and functional, cognitive and trauma symptoms.

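### Alpha = 0.005 on the relapse test belongs to no named family and does not fit n = 72: power is at most about 51–55%, not 80%

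*Protocol article*

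**What the plan says.** Computation of sample size takes relapse over 24 months of follow-up as the dependent variable. It sets the significance level "using an alpha = 0.005 instead of 0.05 to allow correction for multiple comparisons", without naming those comparisons. "The number of patients required to detect a hazard ratio = 2" "in a Cox regression with a statistical power of 80% and alpha = 0.005" is given as "36 per intervention group (two groups, EMDR and ST, equals to a total" of 72. Then, "Assuming a percentage of dropouts of about 10–15% of the participants", the plan is to "recruit approximately 82 patients, 41 allocated in each intervention arm".

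Statistical analysis assigns Cox regression to time to relapse, which it calls the main hypothesis. For the rest, "the hypotheses of the changes in the scores of clinical scales as compared to baseline will be tested using repeated measures analyses of variance", with time, arm and their interaction in the model. The 0.005 does not reappear there.

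The article is not consistent on what is primary:

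- The Abstract has a reduction of affective episodes at 12 and 24 months as primary. It puts affective symptoms, cognition and functioning under the secondary outcome.
- Trial design lists relapses, trauma symptoms, cognition and psychosocial functioning together as primary outcome variables. It keeps course and prognosis as secondary.
- Study aim states hypotheses for relapse at 12 and 24 months, and for symptoms, cognition and functioning at 6, 12 and 24 months.

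**The concern.** A corrected alpha means something only relative to a family of tests. Here the family is not named. Which outcomes could belong to it depends on whether one reads the Abstract or Trial design. If relapse is the only primary, the tenfold stricter level has no stated reason. If there are several primaries, the reader cannot tell which of them share the 0.05.

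The level also has to agree with the sample size computed from it. If 72 patients do not give 80% power at 0.005, the trial is underpowered by its own standard. A relapse result with p between 0.005 and 0.05 would then count as a failure in a study whose size appears to have been set for 0.05.

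**Working it through.** **Inputs from Computation of sample size:** hazard ratio 2, power 80%, alpha 0.005, 1:1 allocation, 72 evaluable patients. Sidedness is not stated; two-sided is taken, with one-sided as a check. The relapse probability is not stated either. With time to relapse as outcome, each patient contributes at most one event, so 72 patients give at most 72 events.

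**Step 1: reproduce the stated n.** With z(power) = 0.842:

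- Schoenfeld: d = 4 (z(1−α/2) + z(power))² / (ln HR)²
- Freedman: d = (z(1−α/2) + z(power))² × ((HR + 1)/(HR − 1))²

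At α = 0.005 two-sided, z = 2.807 and the squared sum is 3.649² = 13.31.

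- Schoenfeld: 4 × 13.31 / 0.4805 = 110.8, so 111 events.
- Freedman: 13.31 × 9 = 119.8, so 120 events.

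One-sided 0.005 gives 98 and 106. None of these is 72.

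At α = 0.05 two-sided, z = 1.960 and the squared sum is 2.802² = 7.85.

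- Schoenfeld: 4 × 7.85 / 0.4805 = 65.3, so 66 events.
- Freedman: 7.85 × 9 = 70.6, so 71 events. This is 36 per arm if every patient relapses, and it matches the stated figure.

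**Step 2: power that 72 patients can give.** Power = Φ(√d × ln 2 / 2 − z) for Schoenfeld and Φ(√d / 3 − z) for Freedman. For d = 72, √d × ln 2 / 2 = 2.941 and √d / 3 = 2.828. At 0.005 this is Φ(0.134) = 0.553 and Φ(0.021) = 0.509.

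| Events | α = 0.05 (Schoenfeld / Freedman) | α = 0.005 (Schoenfeld / Freedman) | Loss in points |
|---|---|---|---|
| 72 (all relapse) | 83.7% / 80.7% | 55.3% / 50.9% | 28 / 30 |
| 50 (70% of 72) | 68.8% / 65.4% | 36.1% / 32.6% | 33 / 33 |

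The 70% is an assumption. Background says that almost 70% of patients relapse within 2 to 4 years. The trial requires two to six episodes in the past year, so its own rate may be higher.

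**Step 3: what 0.005 could be correcting for.** The tables of measurements and the eligibility scales give nine repeatedly measured outcome scales: YMRS, BDRS, CGI-BP-M, CAPS, IES-R, SUD, SCIP, MSCEIT and FAST. One model for each plus one Cox regression makes 10 tests, and 0.05/10 = 0.005. Ten independent tests at 0.005 have a family-wise error of 1 − 0.995¹⁰ = 0.049. A Bonferroni family of this kind would therefore be controlled, but the article does not say that this is the family.

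**The case against.** A reader might infer something stronger: that the correction is spent on a single test that does not need it, while 27 scale-by-visit contrasts (nine scales at three visits) go unprotected, so that the family-wise error is out of control. The article does not support this, for four reasons.

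- Trial design names several primary variables, and hypothesis 1 has two time points. Some sharing of alpha could therefore have a reason.
- The planned analysis is one repeated measures model per scale, nine in all. The 27 is a count from the wording of the hypotheses.
- The article nowhere says that the scales will be tested at 0.05. If 0.005 applies to all ten tests, the family is controlled. The level may appear in the sample size section simply because that is where the calculation is reported.
- Ordering and adjustment of secondary scales commonly sit in an analysis plan, which is not shown. Nor does the Abstract promise a positive claim in each domain. It says that the results will show whether the therapy is "effective in reducing affective episodes, affective symptoms and functional, cognitive and trauma symptoms".

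It is also fair to say that a strict alpha costs no power in a trial sized for it, and that Bonferroni over a defined family is as legitimate as a fixed sequence.

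All of this stands, and it limits the point. It does not remove what the document itself fixes: an alpha with an unnamed family, a power figure that this alpha does not give with 72 patients, and sections that disagree on the primary outcome.

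**Conclusion.** The point holds in this limited form and should be acted on. The stated 80% power at alpha = 0.005 is wrong for 72 patients. The ceiling is about 51–55%, reached only if all of them relapse, and it falls to about 33–36% with 50 events. The sample size is consistent with alpha = 0.05, not 0.005. Because the trial is not sized for the stricter level, that level costs the relapse test 28 to 33 points of power, for a purpose that the article does not define. Family-wise error for the scales is undefined in this document rather than shown to be uncontrolled.

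The figures assume a two-sided test, proportional hazards, 1:1 allocation and one event per patient. One-sided testing does not rescue the claim: 98 to 106 events would still be needed.

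**What to change.** 1. Reconcile the Abstract, Trial design and Computation of sample size so that time to relapse over 24 months is the single primary outcome.
2. Test it first at two-sided 0.05. Only if it is significant, test a short named list of scales in fixed order or with Holm. Label the remaining scales and visits exploratory. State this alpha and order in Statistical analysis.
3. Restate the power from expected events: about 81–84% at 0.05 only if all 72 relapse, and about 65–69% with 50 events. Moving to 0.05 does not by itself secure 80%, which needs 66 to 71 events, or 92–99% of 72 patients. The assumed relapse probability therefore has to be stated and justified.
4. If 0.005 is kept instead, name the family and restate the power as at most about 51–55% with 72 patients. Keeping 80% as well would take at least 111–120 patients before dropout, and 159–172 if 70% relapse.

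Steps 1 to 3 change wording only. However, recruitment began in July 2016, so relaxing the primary alpha should be a dated amendment, made before unblinding. The statistical cost is that the scale results become exploratory if the relapse test fails.

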## Background

Bipolar disorder (BD) is a serious neuropsychiatric condition of major public health importance with a complex multifactorial etiology, involving both genetic and environmental factors and associated with high mortality by suicide. BD is characterized by chronic instability of mood, circadian rhythm disturbances and continual fluctuations in energy levels, affect, sleep and cognitive appraisal of the self and others [1]. Although the disorder is conventionally characterized as being episodic in nature, with full recovery between periods of mania and depression, recent data suggest that many bipolar patients do not obtain a complete remission but continue to experience subsyndromal manic or depressive symptoms [2]. This is a clinically important issue since (1) subsyndromal symptoms are associated with a higher risk of relapses and poorer social functioning [3] and (2) interepisode affective instability seems to be refractory to pharmacological treatment [4]. Further possible risk factors for relapses include substance abuse, comorbid anxiety disorders, personality disorders or physical diseases [5].

The intervention strategies available for BD include essentially pharmacotherapy but also, increasingly, psychosocial interventions such as cognitive behavioral therapy, psychoeducation, interpersonal and social rhythm therapy, and family intervention [6]. However, despite the everyday use in clinical practice of both types of intervention, almost 70% of BD patients suffer from at least one affective relapse within 2 to 4 years [7–9].

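### The stated 36 patients per arm cannot give 80% power for a hazard ratio of 2 at alpha = 0.005; the number fits alpha = 0.05 instead

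*Protocol article*

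**What the plan says.** The sample size paragraph of the Protocol article (Computation of sample size) names the method, "The calculation of the sample size was based on a survival analysis using the statistical package" powerSurvEpi for R, and the significance level, "using an alpha = 0.005 instead of 0.05 to allow correction for multiple comparisons". The target is given as "The number of patients required to detect a hazard ratio = 2", "in a Cox regression with a statistical power of 80% and alpha = 0.005", and the answer as 36 per intervention group, 72 in total. This is raised to about 82 (41 per arm) for 10–15% dropout. Sidedness, the number of events and the assumed relapse probability are not given.

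The Statistical analysis section fixes the matching test: "The main hypothesis of the change in the time to relapse (in weeks) will be analyzed using Cox regressions". The only relapse figure in the article is in the Background: "almost 70% of BD patients suffer from at least one affective relapse within 2 to 4 years".

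**The concern.** Power in a Cox comparison of two arms is driven by the number of events, and a tenfold stricter alpha raises that number considerably. A total of 72 patients looks too small for a hazard ratio of 2 at 0.005 whatever the relapse rate. The level is stated twice and contrasted with 0.05, so a single typing slip is unlikely.

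This paragraph is the only justification of the trial's size on its main outcome. If 0.005 is the operative level, the trial has much less than the stated 80% power to detect a doubling of the hazard. If 0.05 is the operative level, the multiplicity allowance that the paragraph claims does not exist. A reader cannot tell which applies, and the choice should not be left until results are known.

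**Working it through.** **Inputs.** From Computation of sample size: hazard ratio 2, power 80%, alpha 0.005, 1:1 allocation, N = 72 before dropout and 82 after. Not given, so assumed and ranged: sidedness (two-sided as the main case, one-sided also tried) and the proportion relapsing by 24 months (70–100% of both arms combined). The lower value borrows the Background figure, which covers 2 to 4 years. One event per patient is assumed, which is the natural reading of time to relapse in the Statistical analysis section.

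**Formulas.** With z_a and z_b the normal quantiles for alpha and power:

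- Schoenfeld events = 4(z_a + z_b)² / (ln HR)²; here (ln 2)² = 0.4805.
- Freedman events = [(HR + 1)/(HR − 1)]² (z_a + z_b)² = 9(z_a + z_b)².
- Patients = events / proportion relapsing.

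**Step 1: try to reproduce 36 per arm at the stated alpha.**

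- Two-sided 0.005: (2.807 + 0.842)² = 13.31. Schoenfeld 4 × 13.31 / 0.4805 = 110.8, so 111 events; Freedman 9 × 13.31 = 119.8, so 120 events. If every patient relapses this is 56 or 60 per arm; at 70% relapsing it is 80 or 86.
- One-sided 0.005: (2.576 + 0.842)² = 11.68. Schoenfeld 97.2 events, Freedman 105.1. If every patient relapses this is 49 or 53 per arm.

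For 72 patients to suffice, the proportion with an event would have to be between 97.2/72 = 135% and 119.8/72 = 166%. No variant at 0.005 reproduces the figure.

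**Step 2: try alpha 0.05.** Two-sided, (1.960 + 0.842)² = 7.85.

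- Freedman: 9 × 7.85 = 70.6 events; 70.6/2 = 35.3, rounded up to 36 per arm if every patient relapses. This is the stated figure exactly.
- Schoenfeld: 65.4 events, which is 33 per arm if all relapse, and 72 patients at 65.4/72 = about 91% relapsing.
- One-sided 0.05 needs 51.5 (Schoenfeld) or 55.6 (Freedman) events, which is 72 patients at about 71% or 77% relapsing.

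The dropout step is consistent: 72/(1 − 0.12) = 81.8, so 82.

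**Step 3: power for hazard ratio 2 with the stated N.** Schoenfeld power = Φ(√d · ln 2 / 2 − z_a); Freedman power = Φ(√d / 3 − z_a), with d the number of events. Two-sided results, Freedman to Schoenfeld:

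| Patients | Relapsing | Events d | Alpha 0.005 | Alpha 0.05 |
|---|---|---|---|---|
| 72 | 70% | 50.4 | 33–36% | 66–69% |
| 72 | 100% | 72 | 51–55% | 81–84% |
| 82 | 70% | 57.4 | 39–43% | 71–75% |
| 82 | 100% | 82 | 58–63% | 86–88% |

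Worked example, 72 events at 0.005: Schoenfeld 8.485 × 0.3466 − 2.807 = 0.134, so 55%; Freedman 8.485/3 − 2.807 = 0.021, so 51%.

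One-sided 0.005 gives 42–64% with 72 patients over the same relapse range. With 82 patients all relapsing, Schoenfeld gives 3.138 − 2.576 = 0.563, so 71%, the most favourable case.

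A log-rank simulation (exponential times, 36 per arm, 10,000 runs per setting, two-sided 0.005) gave 51% with all relapsing and 35% with about 70% relapsing.

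**Step 4: hazard ratio detectable with 80% power at two-sided 0.005 (Schoenfeld).** exp(2 × 3.649/√72) = 2.36 with 72 events; exp(2 × 3.649/√50.4) = 2.80 with 50.4 events.

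**The case against.** The core arithmetic has no good defence. A separate analysis plan cannot cure it, because alpha, power, hazard ratio and N are stated together in the article. Several qualifications are fair.

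- **How 36 was obtained.** A reader might infer that the figure arises only at 0.05 with every patient relapsing, and hence that non-relapsing patients were ignored. The documents do not support that. Step 2 shows other routes to about 72 at alpha 0.05, and the article gives neither the function nor the event probability. What is firm is that no route at 0.005 leads there. That the correction was not applied is a strong inference, not a documented fact.
- **The power range.** A reader might take 33–55% as the trial's true power. It is conditional on a two-sided test, 72 analysed patients and 70–100% relapsing. An intention-to-treat analysis with multiple imputation is planned, so the 82-patient figures may be nearer. At 60% relapsing, 72 patients give only 27–30%.
- **The 70% value.** It describes bipolar patients generally over 2 to 4 years, while entry here requires two to six episodes in the last year, so a higher 24-month proportion is plausible. The 100% case already grants this in full, and 80% is still not reached.
- **One event per patient.** The Abstract and Study aim speak of fewer episodes or relapses, so time to first relapse is a reading. It is the natural one for the Cox regression of time to relapse that the plan specifies.
- **Simply adopting 0.05.** This is not free. The stricter alpha has a stated purpose, and Trial design lists relapses, trauma symptoms, and cognition and psychosocial functioning as primary outcome variables.

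**Conclusion.** Wrong as written. The combination of alpha 0.005, 80% power, hazard ratio 2 and 36 per arm is impossible under either standard formula, one- or two-sided, at any relapse proportion up to 100%, given one event per patient. The shortfall is large: at least 97 events are needed against at most 72 available. The number fits alpha 0.05, so the multiplicity correction appears to have been described but not carried into N.

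The size of the power loss depends on inputs that the article does not state. Two-sided at 0.005 with 70–100% relapsing, power is about 33–55% for 72 patients and 39–63% for 82. The most favourable case (one-sided, all 82 relapsing) reaches about 71%.

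**What to change.** Reconcile alpha, power and N in Computation of sample size, and state the sidedness, the required number of events and the assumed 24-month relapse proportion. Enrolment need not change. Then take one of two routes, before any outcome comparison between arms is seen:

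- **If 0.005 is kept:** replace 80% with the power that the design delivers (about 33–55% for 72 patients, two-sided, 70–100% relapsing). Alternatively, state that 80% power applies to a hazard ratio of about 2.4–2.8 (Schoenfeld) rather than 2.
- **If the calculation was in fact at 0.05:** say so, and give the two-sided power for 72 patients (about 66–69% at 70% relapsing, 81–84% if all relapse). Withdraw the statement that N allows for multiple comparisons, and reconcile this with the several primary outcome variables listed in Trial design.

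The first route costs only wording and a less favourable stated power. The second also obliges the sponsor to settle the outcome hierarchy. Because recruitment has begun (Trial status), the reason for the less strict level should be recorded.
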